#### Nested mechanistic study

The nested study will recruit a sub-sample of participants from the main RCT. No group x time interaction is hypothesised to occur for the primary dependent variable of quadriceps femoris muscle volume. Therefore, a within factors priori power analysis was performed to calculate the sample size required to detect a within group change in quadriceps femoris muscle volume between T1 and T2. Based on data from the ADAPT pilot study [26], which reported an effect size of *d* = 0.35, the minimum sample size required is *n* = 52. By estimating an approximate 20% dropout rate we concluded a sample size of *n* = 64 (*n* = 32 in each intervention arm) is required.

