#### Nested mechanistic study

2)The nested mechanistic study will compare the effects of the two interventions on i) muscle morphology and architecture, ii) muscle strength, iii) performance during occupational specific tasks, iv) kinetic and kinematic variables during functional tasks and v) blood biomarkers of EIMD, inflammation, oxidative stress and vascular function.

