### Sample size

#### Main randomised control trial

A sample size of 150 participants (75 in each arm) will be recruited into the study. The study is powered to detect a minimum clinically important difference (MCID) in the Lower Extremity Functional Scale (LEFS) using a between group MCID of 9 points and an estimated standard deviation of 15.8 [61]. From this an effect size, f, of 0.285 was calculated. The expected sample size for 0.80 power to detect an effect size (f) of 0.285 at a level of significance α = 0.05 is 122 participants (61 In each group). By estimating an approximate 20% dropout rate we concluded a sample size of 150, with 75 in each intervention arm. The G Power 3.1.9.7 software was used to calculate the sample size. This sample size is also sufficient to detect a MCID of 8 points in the KOOS ADL subscale with a statistical significance of *α* = 0.05 and power of > 0.80 where the MCID is 8 points and expected standard deviation is 8.9 [122, 123].

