### Statistical methods and analysis

Descriptive data will be reported as the mean and standard deviation (SD) for continuous variables and frequency statistics for non-continuous variables. Prior to statistical analysis, tests to establish the normality of data distributions will be performed and, where appropriate, variance-stabilising transformations will be applied. Analysis will be conducted on a modified intention to treat basis, including all available outcomes at course discharge regardless of compliance to treatment. All tests will be two-sided, and alpha will be set at 0.05. Assumptions for all tests will be considered and adhered to. In the primary analysis, a mixed-effects regression analysis will be used to assess the effects of the interventions on primary outcome scores at course discharge (T2) between the two treatment groups, after adjusting for fixed effects of biological sex at birth and baseline (T1) primary outcome scores, with study site centre included as a random effect. The treatment effect estimates will be presented from the adjusted mixed model with 95% confidence intervals (CI) and P-values. This mixed-effects model will be used for all secondary outcome measures. Supporting analysis of the primary outcome will include: A per-protocol analysis including patients with compliance > 80% to intervention; a repeat of the primary analysis with additional adjustments for baseline values and a mixed effects model to compare primary outcomes at three-months post intervention between the two treatment groups. In addition to the primary adjusted analysis, the unadjusted mean differences between groups will be compared using t-test for independent groups, reporting 95% CI. Sub-group analysis will be conducted by diagnostic sub-group, biological sex at birth, age and pain levels at baseline. Study participant flow will be recorded and reported in accordance with the Consolidated Standard of Reporting Trials (CONSORT) guidelines. Analysis will be conducted on a pairwise case basis. Therefore, all missing data will be reported, and patterns investigated. Sensitivity analysis will be conducted using multiple imputation techniques to assess the effect of missing data on primary outcomes. Post intervention adverse events between groups using Fisher’s exact test. All analysis will be conducted using SPSS.

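### The nested study's 52 participants can support only a change pooled over both arms; the test behind the figure is not stated, and no calculation covers the aim of comparing the arms

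*Protocol article*

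**What the plan says.** Under Study aims, the "nested mechanistic study will compare the effects of the two interventions", and muscle morphology and architecture head the list of outcomes.

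Under Sample size, Nested mechanistic study, the reasoning is different. No group-by-time "interaction is hypothesised to occur for the primary dependent variable of quadriceps femoris muscle volume", and for that reason a "power analysis was performed to calculate the sample size required to detect a within group change in quadriceps femoris muscle volume" between T1 and T2. The effect size comes from the pilot, "which reported an effect size of *d* = 0.35, the minimum sample size required is *n* = 52". An allowance of about 20% dropout takes this to 64, or 32 per arm. The paragraph gives no power, alpha, sidedness, standardiser for d or pre-post correlation.

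Two other places supply candidate inputs. The main-trial calculation reads "The expected sample size for 0.80 power to detect an effect size (f) of 0.285 at a level of significance" 0.05. Under Statistical methods and analysis, "All tests will be two-sided, and alpha will be set at 0.05". That section's model compares the two groups at T2, adjusted for the T1 value, and is extended to all secondary outcomes.

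**The concern.** There are two separate difficulties.

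First, the printed figure cannot be tied to a test. The simplest paired calculation that returns 52 is one-sided, whereas the analysis section makes every test two-sided. The target is a change within a group, yet the total is then halved between the arms, so each arm holds about half the number calculated.

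Second, the quantity that was sized is not the quantity the nested study sets out to learn. Both arms follow the same standardised three-week course, so a pre-post change over everyone could arise from that course alone and does not separate the two forms of resistance training.

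What is at stake is the interpretation of the quadriceps volume result. The expected finding is no interaction. With a small sample and no precision or equivalence basis, a non-significant arm comparison would be weak evidence of anything, and the article gives the reader no way to see that.

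**Working it through.** **Inputs.** From the nested sample size paragraph: d = 0.35, two time points, n = 52, then 64 (32 per arm). From the analysis section: alpha 0.05, two-sided. Assumed: power 0.80, which is stated only for the main trial. Completers per arm: 52/2 = 26.

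**Formula.** For a paired test with standardised change d_z, T = mean change/(SD of change/√n) is noncentral t with n − 1 degrees of freedom and noncentrality d_z√n. Power is the probability that T exceeds the critical value (one-sided), or that its absolute value does (two-sided).

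**Step 1: reproduce 52, with d_z = d = 0.35.**
- One-sided: n = 51 gives 0.794 and n = 52 gives 0.801. The required n is 52, an exact match.
- Two-sided: n = 66 gives 0.7999 and n = 67 gives 0.806. The required n is 67.
- Two-sided power is 0.70 at n = 52, and 0.79 if all 64 are retained.

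**Step 2: let d be scaled by the raw SD.** Then d_z = d/√(2(1 − ρ)), where ρ is the unstated pre-post correlation. A two-time-point within-factor F-test with f = d/2 = 0.175 has noncentrality f²·2n/(1 − ρ) = n·d_z², so it is the same calculation for a single group.

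| Assumed ρ | d_z | n for 0.80, two-sided | Two-sided power at 52 |
|---|---|---|---|
| 0.3 | 0.296 | 92 | 0.55 |
| 0.5 | 0.350 | 67 | 0.70 |
| 0.6 | 0.391 | 54 | 0.79 |
| 0.61 | 0.396 | 52 | 0.80 |
| 0.7 | 0.452 | 41 | 0.89 |

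So 52 is also a two-sided answer, but only at ρ near 0.61. With two groups in the F-test, ρ = 0.61 again gives 52 (power 0.800).

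**Step 3: power within one arm**

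| Reading | 26 in the arm | 32 in the arm (no dropout) |
|---|---|---|
| d_z = 0.35, two-sided (the stated rule) | 0.40 | 0.48 |
| d_z = 0.35, one-sided (returns 52) | 0.54 | 0.61 |
| Raw-SD d, ρ = 0.61, two-sided (returns 52) | 0.49 | 0.58 |

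Neither reading that returns 52 gives an arm of 26 more than 0.54. The lower end, 0.40, is what the one-sided reading becomes once the two-sided rule is applied.

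**Step 4: precision of the arm comparison.** Unadjusted, with 26 per arm, the 95% CI half-width in SD units is t(0.975, 50) × √(2/26) = 2.009 × 0.277 = 0.56. Adjustment for T1 multiplies this by about √(1 − ρ²):
- ρ = 0.7: 0.557 × 0.714 = 0.40 SD
- ρ = 0.9: 0.557 × 0.436 = 0.24 SD

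**The case against.** A reader might infer that 52 can arise only from a one-sided test, and therefore that the sample size breaks the two-sided rule. The article does not support that. It never says one-sided, it describes a within-factors analysis, and the non-directional F-test returns 52 at a correlation near 0.61. A three-time-point version at correlation 0.7 and 0.95 power also returns 52, although that does not fit the stated T1-T2 contrast. One-sidedness is a plausible explanation, not an established one. For the same reason 0.70 is conditional on how d was standardised, and the pilot is not available to settle it. This objection stands and limits the point.

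It may also be said that the within-group basis is declared openly and justified by the hypothesis of no interaction. That is true, but expecting no interaction is not a reason to leave the arm comparison without any statement of precision.

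A reader might further infer that the authors intend to report a null interaction as equivalence. Nothing in the article says so, and its analysis section already promises estimates with 95% confidence intervals. The risk is one of later interpretation.

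Finally, baseline adjustment makes the arm comparison better than the unadjusted 0.56 SD suggests, perhaps much better for a stable measure such as muscle volume. The dropout rounding (64 × 0.8 = 51.2 against 52) is trivial under an approximate 20% rate and is not part of this point.

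**Conclusion.** The point holds in a limited form. The nested sample size is under-specified, and its wording does not match what it can deliver.

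- **Pooled change.** If d is the paired standardised change and 0.80 power was intended, two-sided power is about 0.70 with 52 completers (0.79 with all 64), and 67 completers would be needed. If d uses the raw SD, power at 52 runs from 0.55 to 0.89 for correlations of 0.3 to 0.7.
- **Change within an arm.** Power is about 0.40 to 0.54 for 26 under the T1-T2 readings that return 52 at 0.80 power. A higher correlation would raise it (0.60 at 0.7), but the calculation would then have returned 41. The size therefore supports only a change pooled over both arms.
- **Comparison of arms.** No calculation is given. The half-width is about 0.56 SD unadjusted, and about 0.40 or 0.24 SD with T1 adjustment at assumed correlations of 0.7 or 0.9.

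This is worth correcting but does not threaten the main trial. It concerns a sub-study, and the LEFS primary outcome has its own sample size calculation.

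**What to change.** Keep the 64 participants and amend the text.

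1. In the nested sample size paragraph, say that the calculation concerns the T1-T2 change in quadriceps volume pooled over both arms. Give its sidedness, power, the standardiser of d and any pre-post correlation used.
2. Restate the power under the two-sided rule: about 0.70 pooled and 0.40 per arm for 52 completers if d is the paired standardised change, otherwise the values for the correlation actually used.
3. State that the between-arm difference in T2 quadriceps volume, adjusted for T1, will be reported as an estimate with its 95% CI, and give the expected half-width with the correlation assumed.
4. State that a non-significant group-by-time interaction will not be read as similarity or equivalence of the two interventions.

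The cost is a few sentences and possibly a less favourable stated power. No extra participants or measurements are needed.

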### Statistical methods and analysis

Descriptive data will be reported as the mean and standard deviation (SD) for continuous variables and frequency statistics for non-continuous variables. Prior to statistical analysis, tests to establish the normality of data distributions will be performed and, where appropriate, variance-stabilising transformations will be applied. Analysis will be conducted on a modified intention to treat basis, including all available outcomes at course discharge regardless of compliance to treatment. All tests will be two-sided, and alpha will be set at 0.05. Assumptions for all tests will be considered and adhered to. In the primary analysis, a mixed-effects regression analysis will be used to assess the effects of the interventions on primary outcome scores at course discharge (T2) between the two treatment groups, after adjusting for fixed effects of biological sex at birth and baseline (T1) primary outcome scores, with study site centre included as a random effect. The treatment effect estimates will be presented from the adjusted mixed model with 95% confidence intervals (CI) and P-values. This mixed-effects model will be used for all secondary outcome measures. Supporting analysis of the primary outcome will include: A per-protocol analysis including patients with compliance > 80% to intervention; a repeat of the primary analysis with additional adjustments for baseline values and a mixed effects model to compare primary outcomes at three-months post intervention between the two treatment groups. In addition to the primary adjusted analysis, the unadjusted mean differences between groups will be compared using t-test for independent groups, reporting 95% CI. Sub-group analysis will be conducted by diagnostic sub-group, biological sex at birth, age and pain levels at baseline. Study participant flow will be recorded and reported in accordance with the Consolidated Standard of Reporting Trials (CONSORT) guidelines. Analysis will be conducted on a pairwise case basis. Therefore, all missing data will be reported, and patterns investigated. Sensitivity analysis will be conducted using multiple imputation techniques to assess the effect of missing data on primary outcomes. Post intervention adverse events between groups using Fisher’s exact test. All analysis will be conducted using SPSS.

At *n* = 20 an interim analysis of study fidelity and reliability of data recorded will be performed. At *n* = 50 and *n* = 100 additional interim analysis will be performed to establish any clear superiority of one intervention over another. If the magnitude of the difference warrants consideration for stopping the trial, this will be discussed with the chair of the MOD ethics committee.

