#### Patient reported outcome measures

The Lower Extremity Functional Scale (LEFS) at course discharge (T2) will be the primary outcome measure. The LEFS is a patient-reported outcome measure (PROM) that measures functional status in patients with lower limb MSKI [61]. Ability to perform 20 activities, ranging from walking to running on uneven ground, are self-reported from 0–4 with higher scores indicating better function. The minimum clinically important difference (MCID) of the LEFS is 9 points. The LEFS is a validated tool and has demonstrated good test-retest reliability and responsiveness in individuals with persistent knee pain [61–63].

Secondary patient reported outcome measures will record patient reported levels of function, pain, fear of movement, rehabilitation beliefs, physical activity and occupational status. Questionnaires include: the Knee Injury and Osteoarthritis Outcome Score (KOOS) [64], Patient Specific Functional Scale [65], Musculoskeletal Health Questionnaire (MSKHQ) [66], Tampa Scale of Kinesiophobia (TSK) [67], Numeric Pain Rating Scale (NPRS) [68], Functional Activity Assessment (FAA) [69], Sports Injury Rehabilitation Beliefs Survey (SIRBS) [70] and the International Physical Activity Questionnaire (IPAQ). Questionnaires will be distributed at T1, T2 and T3 via email using a research electronic data collection application (REDCap).

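### The plan leaves room to choose the scale of the primary LEFS estimate after testing the data for normality, although the MCID and power are fixed at 9 raw points

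*Protocol article*

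**What the plan says.** In the Protocol article, Statistical methods and analysis, a preparatory step precedes the models: "tests to establish the normality of data distributions will be performed and, where appropriate, variance-stabilising transformations will be applied". It is written for all outcomes. It names no transformation, does not set LEFS apart, and does not require a return to LEFS points. The same section then takes the treatment effect, its 95% CI and its P-value from the adjusted mixed model, and adds an unadjusted comparison of means by t-test. It also says in general terms that the assumptions of the tests will be considered.

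Elsewhere everything is in raw points. Under Patient reported outcome measures, "The Lower Extremity Functional Scale (LEFS) at course discharge (T2) will be the primary outcome measure"; its 20 items "are self-reported from 0–4 with higher scores indicating better function"; and "The minimum clinically important difference (MCID) of the LEFS is 9 points". Under Sample size, Main randomised control trial, the calculation is made "using a between group MCID of 9 points and an estimated standard deviation of 15.8".

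**The concern.** The target difference and the power are set in LEFS points, but the scale of the reported estimate is left open until the data have been inspected. If LEFS were transformed, the main coefficient and its interval would be in units for which the article gives neither an MCID nor a power basis.

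The step also addresses the wrong quantity. The mixed model assumes something about residuals, not about the distribution of the raw scores. Raw scores can look non-normal because of baseline, sex or treatment differences while the residuals are acceptable. A variance-stabilising transformation is, moreover, a remedy for unequal variance, which a normality test does not examine.

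At stake are the readability of the primary result against 9 points and the pre-specification of its scale.

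**Working it through.** **Inputs from the protocol article.** Target difference 9 points and SD 15.8 (Sample size); 20 items scored 0–4, so a range of 0 to 20 × 4 = 80 (Patient reported outcome measures); 122 evaluable participants, 61 per arm (Sample size); two-sided alpha 0.05 (Statistical methods and analysis). **Assumed, because the article gives none:** the LEFS mean at discharge (50, 55, 60 or 65), the shape of the distribution, the form of any transformation, and Shapiro-Wilk at 5% as the normality test.

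**1. The plan's own figures.** f = 9 / (2 × 15.8) = 0.285, as stated. This confirms that the power basis is in raw points. The stated 122 does not follow from it for two arms. The normal approximation gives 49 per arm (98 in total) and the exact F test with 1 numerator df gives 99. The figure of 122 matches 2 numerator df. With 61 per arm, power for 9 points is about 0.88 rather than 0.80. This is a separate matter; it overstates the need and does not weaken the raw-scale analysis.

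**2. What 9 points becomes after transformation.** On a reflected square root, √(80 − x):
- 50 to 59: √30 − √21 = 5.48 − 4.58 = 0.89
- 65 to 74: √15 − √6 = 3.87 − 2.45 = 1.42

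Other common choices show the same (absolute difference for a 9-point step):

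| Step | log x | √x | log(81 − x) | arcsine √(x/80) |
|---|---|---|---|---|
| 35 to 44 | 0.229 | 0.717 | 0.218 | 0.113 |
| 45 to 54 | 0.182 | 0.640 | 0.288 | 0.116 |
| 55 to 64 | 0.152 | 0.584 | 0.425 | 0.130 |
| 65 to 74 | 0.130 | 0.540 | 0.827 | 0.170 |
| Largest / smallest | 1.8 | 1.3 | 3.8 | 1.5 |

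No column is constant, so no single transformed value stands for the MCID. In the other direction, a log-scale effect returns as a ratio. The ratio 59/50 = 1.18 is 9 points at 50, but 30 × 0.18 = 5.4 points at 30 and 65 × 0.18 = 11.7 points at 65.

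**3. Would a normality test reject?** Normal scores with SD 15.8 were rounded and clipped to 0–80, with 3,000 runs at N = 122. The means are those before clipping.

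| Assumed mean | Shapiro-Wilk rejects at 5% |
|---|---|
| 50 | 15% |
| 55 | 68% |
| 60 | 99% |
| 65 | 100% |

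The answer depends almost wholly on a mean that the article does not give.

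**4. Is transformation needed for validity?** Under the same assumptions, with 61 per arm, no treatment effect and 5,000 runs, the raw-scale t-test rejected in 4.4% to 5.2% of runs across the four means, against a nominal 5%. For scale, the unadjusted 95% CI half-width at 60 per arm is 1.980 × 15.8 × √(2/60) = 5.7 points, directly readable against 9. Baseline adjustment should narrow it.

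**The case against.** The case on the other side has weight.

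- **The tests do not strictly decide.** A reader might infer a mechanical two-stage rule in which rejection forces a transformation. The text does not say that: transformation is applied only where judged suitable. This stands. But judgement exercised after seeing the data is still a data-dependent choice of scale.
- **The sentence is a general preamble.** It covers blood biomarkers, imaging, force data and questionnaires alike, and for some of these transformation is routine. The wording on the primary model speaks of outcome scores, and an unadjusted mean difference is promised, which may well supply a result in points. This stands in part. Neither analysis is exempted from the preparatory step, and the headline estimate comes from the adjusted model.
- **Detail belongs in an analysis plan that is not shown.** Naming the transformed outcomes and the back-transformation rule does belong there, and their absence is not the point. The point is the step that the article itself states.
- **Assumption checks are promised.** The general statement on assumptions can reasonably include residuals. It does not withdraw the test on the data distributions.
- **A transformed effect can still be related to points.** Predictions can be back-transformed at chosen baselines. What holds is narrower: the coefficient has no constant equivalent in points.

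A reader might also infer that rejection is likely because the score has a ceiling, or that the comparison would be biased. The documents support neither. They give no discharge mean, and no bias or type I error inflation has been shown. Nor does the article formally make 9 points a threshold for interpreting the result; it defines the MCID and uses it for power.

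**Conclusion.** The point holds in a limited form. The article allows the scale of the primary LEFS estimate to be chosen after the data are inspected, while its MCID and power are tied to 9 raw points. If LEFS were transformed, the equivalent of 9 points would vary with the starting score, by a factor of 1.3 to 3.8 over the steps and transformations examined. Whether this would happen is unknown: the simulated rejection rate runs from about 15% to 100% for assumed means of 50 to 65, and a rejection would still need a decision to transform. These rates rest on the clipped-normal model and on Shapiro-Wilk as the test.

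The consequence is a possible loss of interpretability and of pre-specification for the primary result. The transformation would buy little, because the raw-scale comparison keeps its error rate under the same assumptions. The correction is worth making because it is cheap. It does not affect the sample size.

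**What to change.** State in Statistical methods and analysis that the primary LEFS analysis is carried out and reported in untransformed points, whatever the normality tests show. Replace the test on the data distributions, for this outcome, by a check of the model residuals. If these are clearly non-normal or heteroscedastic, add heteroscedasticity-robust or bootstrap 95% CIs on the raw scale as a sensitivity analysis; any transformed analysis of LEFS is likewise sensitivity only. Keep transformation for outcomes named in advance, such as blood biomarkers.

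The cost is about one sentence and one extra sensitivity run. What is given up is the option of a transformed primary analysis.

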#### Randomisation

A permuted block randomisation method with a 1:1 ratio of the two treatment arms will be used using random block sizes. Randomisation will be stratified by study site, biological sex at birth, and diagnostic sub-group. A plain language statement will inform participants that they have an equal chance of receiving the HL-RT or LL-BFR intervention. A concealed list will be used to assign group allocation, this will be performed by an independent administrator not involved in the recruitment, treatment, or assessment of study outcomes.

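### Diagnostic sub-group stratifies the randomisation but is missing from the primary model, so the reported standard error may be slightly too large

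*Protocol article*

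**What the plan says.** Under Randomisation, the protocol article states: "Randomisation will be stratified by study site, biological sex at birth, and diagnostic sub-group". The method is stratified blocking with equal allocation: "A permuted block randomisation method with a 1:1 ratio of the two treatment arms will be used using random block sizes".

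Under Statistical methods and analysis, the primary comparison of T2 LEFS is a mixed-effects regression "after adjusting for fixed effects of biological sex at birth and baseline (T1) primary outcome scores". Site is the only other term named in that model, and it enters as a random effect. The same model is to be used for all secondary outcomes.

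Two other statements in that section bear on the point. One supporting analysis is "a repeat of the primary analysis with additional adjustments for baseline values", with the added covariates not named. The other is: "Sub-group analysis will be conducted by diagnostic sub-group, biological sex at birth, age and pain levels at baseline". Diagnostic sub-group is named nowhere else in the analysis section.

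**The concern.** The model is given as a specific covariate list, not as a general statement that the stratification factors will be adjusted for. Two of the three factors are on the list and the third is not. The gap therefore lies between two statements in the article itself, and is not a detail left to a later analysis plan.

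Blocking within diagnostic sub-group makes the arms similar in diagnosis. Variation in outcome between diagnoses then largely cancels from the difference between arms. A model without diagnosis still counts that variation as residual noise, so it reports a standard error larger than the true variability of the estimate. At stake are the width of the LEFS confidence interval, the true size of the nominal 5% test and a little power. Every secondary outcome analysed with the same model is affected in the same way, to a degree that depends on how far diagnosis predicts that outcome.

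**Working it through.** **The two lists side by side**

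| Factor | Randomisation | Primary model |
|---|---|---|
| Study site | stratified | random effect |
| Sex at birth | stratified | fixed effect |
| Diagnostic sub-group | stratified | absent |
| Baseline LEFS | not stratified | fixed effect |

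**Inputs from the protocol article**
- Sample size, main RCT: the trial is powered "using a between group MCID of 9 points and an estimated standard deviation of 15.8". This gives f = 9/(2 × 15.8) = 0.285, as the article states.
- The same section recruits 150 and allows about 20% dropout: 150 × 0.80 = 120 evaluable, or 60 per arm.
- Statistical methods and analysis: "All tests will be two-sided, and alpha will be set at 0.05".

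The plan gives no figure of its own for the effect of leaving diagnosis out.

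**Assumptions not in the documents**
- q, the share of residual T2 LEFS variance that diagnosis explains after baseline LEFS, sex and site: 0% to 10%.
- ρ, the correlation between baseline and T2 LEFS: 0, 0.5 or 0.7. With ρ = 0 the full SD of 15.8 is used.
- Diagnosis exactly balanced between arms.

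**Formulas** (normal approximation)
- Standard error reported without diagnosis: SE = 15.8 × √(2/60) × √(1 − ρ²). This is 2.88 at ρ = 0, 2.50 at ρ = 0.5 and 2.06 at ρ = 0.7.
- True standard error under balance: SE × √(1 − q). Overstatement: 1/√(1 − q) − 1.
- Type I error without diagnosis: 2 × [1 − Φ(1.96/√(1 − q))].
- Power without diagnosis: Φ[(9/SE − 1.96)/√(1 − q)].
- Power with diagnosis: Φ[9/(SE√(1 − q)) − 1.96].

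Worked case, q = 10%, ρ = 0:
- √0.90 = 0.949, so the overstatement is 1/0.949 − 1 = 5.4%.
- Type I error = 2 × [1 − Φ(2.066)] = 0.039.
- 9/2.88 = 3.12, so power is Φ[(3.12 − 1.96)/0.949] = 0.889 without diagnosis and Φ[3.12/0.949 − 1.96] = 0.908 with it.

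**Results**

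| q | SE too large by | Type I error | Power without → with, ρ = 0 | ρ = 0.5 | ρ = 0.7 |
|---|---|---|---|---|---|
| 0% | 0% | 5.0% | 0.877 → 0.877 | 0.950 → 0.950 | 0.992 → 0.992 |
| 2% | 1.0% | 4.8% | 0.879 → 0.883 | 0.952 → 0.953 | 0.993 → 0.993 |
| 5% | 2.6% | 4.4% | 0.883 → 0.893 | 0.954 → 0.959 | 0.993 → 0.994 |
| 10% | 5.4% | 3.9% | 0.889 → 0.908 | 0.958 → 0.967 | 0.994 → 0.996 |

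The overstatement and the type I error depend on q alone. The power gain also depends on ρ. At q = 10% it is 1.9 points at ρ = 0, 0.9 at ρ = 0.5 and about 0.2 at ρ = 0.7.

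**Check by simulation.** The set-up was 120 participants, five sites, two sexes and two assumed diagnostic groups, with stratified blocks of 2 or 4. Site was fitted as a fixed effect, baseline was unrelated to outcome, and there were 4,000 runs under no effect. At q = 10%:

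| | Without diagnosis | With diagnosis |
|---|---|---|
| Mean reported SE | 2.90 | 2.76 |
| Actual SD of the estimate | 2.71 | 2.70 |
| Rejection rate, no true effect | 0.036 | 0.045 |

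At q = 5% the rejection rates were 0.043 and 0.049. Estimates were unbiased under both models. The actual spread of the estimate barely changes, so what the omission distorts is the reported standard error.

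**The case against.** The best case for leaving the model alone has five parts.

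1. **The size rests on an assumption.** The documents do not say how far diagnosis predicts T2 LEFS. Baseline LEFS is already in the model and all participants have mechanical knee pain, so the residual share may be near zero, and at zero nothing changes. This stands, and is why the range starts at 0%.
2. **Balance will not be exact.** Five sites, two sexes and at least two diagnoses make at least 20 strata for 150 participants, with incomplete blocks and about 20% dropout. Imperfect balance among completers reduces the conservatism. This stands. The simulation covers incomplete blocks but not dropout.
3. **The error is on the safe side and power is ample.** Power without the factor is at least 0.877 in every case above, against a target of 0.80. This stands and limits how much the point matters.
4. **The supporting analysis may already include diagnosis.** It might, but its covariates are unnamed and it is not the primary analysis, so it does not close the gap.
5. **Diagnosis is examined in a sub-group analysis.** That analysis asks whether the treatment effect differs between diagnoses. It does not correct the standard error of the overall effect.

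Stronger readings are tempting but not supported. A reader might infer that the analysis ignores the stratified design; it does not, since site and sex are in the model. A reader might infer that the estimate itself loses precision; stratification has already delivered that precision, and mainly the reported standard error is wrong. A reader might also take the sub-group listing as a sign that the investigators expect diagnosis to be prognostic. It shows no such thing: age and baseline pain are listed there too, and neither is a named covariate of the primary model.

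**Conclusion.** The inconsistency is real: one of three stratification factors is missing from a stated covariate list, without a reason, and nothing else in the article restores it. The consequence is modest and conditional. If diagnosis explains 0% to 10% of residual T2 LEFS variance (assumed) and is balanced between arms, the reported standard error is 0% to about 5% too large. The confidence interval is wider by the same proportion, and the nominal 5% test runs at 5.0% down to about 3.9%. Including the factor gains at most about 2 points of power with the unadjusted SD of 15.8, and under 1 point if baseline and T2 LEFS correlate at 0.5 or more (assumed).

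The treatment estimate is not biased and the false-positive rate is not inflated. The mismatch is certain; its numerical effect is not, and it is nil if diagnosis adds nothing beyond baseline LEFS, sex and site. The effect on secondary outcomes has not been quantified.

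**What to change.** Add diagnostic sub-group, with the categories used in the randomisation, as a fixed effect in the primary model. Carry it into the secondary-outcome, three-month (T3), per-protocol and multiple-imputation models, so that the supporting results differ from the primary one only in the respect each is meant to test. If there is a reason to leave the factor out, state it.

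The cost is one phrase in the analysis section and one degree of freedom per extra category. The variable has to be recorded for randomisation in any case, and the sample size does not change. Settling it before analysis also removes a later choice between models with and without diagnosis.
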